#### Allocation concealment

For the purpose of allocation concealment, the name of each group will be written on a card and placed in opaque envelopes; thereby, 88 envelopes will be prepared on the basis of the predetermined sequence. The envelopes are numbered from 1 to 88. Then the envelopes are sequentially opened for every new participant to determine the group.

### Blinding

Owing to the nature of the study, it is impossible to blind either the participant or researchers.

### Treatment fidelity

One of the researchers (SV) is trained to perform EMDR therapy. Training and monitoring of her performance on implementing the intervention will be carried out by a clinical psychotherapist. To ensure that the intervention is implemented correctly, 15% of the sessions will be randomly evaluated by using the EMDR Fidelity Rating Scale [49].

### Data management

The person (SV) responsible for collecting the data will be trained to monitor the data collection process at all stages of the study. Data entry to the SPSS software will be monitored by ZA and MR.

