This is the desensitization step that targets the thrilling feeling of the participant. In this phase, the participants will be asked to provide their pre-treatment Subjective Units of Anxiety or Distress Scale (SUD) and Validity of Cognition Scale (VOC) scores. Then eye movement sets will be used and the distressing memory of dysmenorrhea will be processed. At the end of the phase, the client reports their level of negative affect by using the SUD.

Phase 5: Installation

This phase focuses on cognitive rehabilitation and reconstruction and on strengthening the positive cognition to replace the negative cognition. In this phase, the researcher will try to install the positive cognition of menstruation without dysmenorrhea in the participant’s mind. The participants will be asked to provide their VOC scores.

Phase 6: Body scan

This phase assesses and evaluates the physical tensions. This step is also called the physical scan. After the positive cognition is installed, the participants will be asked to hold in their mind both the target event (dysmenorrhea) and the positive cognition (menstruation without dysmenorrhea) and then scan their own body mentally from top to bottom. Then they will be asked to identify any remaining discomfort in the form of body sensation.

Phase 7: Closure

The completion or final step consists of interactive reporting and is designed primarily to maintain the balance of the participant in the session and re-evaluate her at the end. In this phase, the participants will reach a state of emotional equilibrium. They will be informed of the possibility of having disturbing images, thoughts, or emotions between the sessions. This is a positive sign and they should not be concerned.

Phase 8: Re-evaluation

This is a reassessment step and its goal is to ensure that all relevant events have been processed [39, 40].

The EMDR therapy would be performed by one of the researchers (SV). She has been trained by a clinical psychotherapist to implement this type of therapy.

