### Measures

In this research, four instruments will be used for data collection:

*The demographic characteristics questionnaire* will be used to collect demographic and reproductive characteristics, including age, menarche age, education level, field of study, every menstrual cycle (length of menstrual period and bleeding period), and medication/drug use history. This questionnaire has been developed on the basis of the objectives of the study and its validity will be examined by the content validity method.

*The VAS* will be used to evaluate the severity of dysmenorrhea pain. An Iranian systematic review confirmed the validity and reliability of VAS for evaluation of dysmenorrheal pain [42]. The VAS is a 100-mm line where the “0” end (0) means completely painless and the other end (10) means the most intense pain imaginable. The patient marks the severity of pain on the line. The simplicity makes it easy to use for the assessment of pain [43].

*SUD* is a self-reporting scale with a 0- to 10-point rating scale. Participants are asked to report their level of distress or anxiety based on SUD scale. A score of 0 indicates the absence of distress, and a score of 10 indicates the maximum level of distress [39]. This scale has been widely used by Iranian researchers and its validity and reliability have been confirmed in their studies [44–46].

*The VOC* shows the level of belief in positive or negative recognition. Similar to the SUD scale, it is self-reporting and represents an individual’s assessment of her or his own cognition. A 7-point rating scale ranging from 1 to 7 is used to evaluate, quantify, and indicate the participant’s self-recognition. A score of 1 means a lack of belief in that particular cognition, and a score of 7 means a full belief in it [39]. This scale has been widely used by Iranian researchers and its validity and reliability have been confirmed in their studies [44–46].

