### Primary outcome

The primary outcomes are the pain intensity, anxiety, or distress in patients with primary dysmenorrhea and their cognition of the dysmenorrhea.

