## Discussion

The present study will be the first randomized clinical trial to investigate the effect of EMDR therapy on pain management in patients with primary dysmenorrhea. The results are expected to provide insight into the safety and efficacy of EMDR therapy in treating primary dysmenorrhea. The strength of the study is its design as a randomized method with good sample size. However, owing to the nature of the intervention, blinding is impossible in this study.

EMDR therapy is a systematic, comprehensive, non-invasive, simple, and evidence-based treatment for unpleasant memories and related events [29]. EMDR therapy has been used to treat various conditions, including anxiety, depression, chronic pain, phantom limb pain, somatization syndrome, and post-traumatic stress disorder syndrome [30–34]. The systematic review by Tesarz et al. (2014) showed that EMDR therapy was effective, safe, and promising in treating chronic and uncomplicated pain [35]. The present study was designed on the basis of the efficacy of EMDR therapy shown in previous study in the management of a range of conditions, including chronic pain and previous unpleasant memories. In the present study, the focus is on the chronic nature of primary dysmenorrhea and the correlation between the trauma due to the initial unpleasant experience of menstruation and associated psychosomatic disturbances, such as anxiety and depression and dysmenorrhea.

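### The EMDR therapist is also responsible for collecting self-reported outcomes, and all blinding is called impossible, so an avoidable arm-dependent courtesy bias is left in the comparison

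*Protocol article*

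**What the plan says.** All references are to the protocol article.

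- **Therapist.** Under Intervention: "The EMDR therapy would be performed by one of the researchers". That researcher is identified by initials, and Treatment fidelity gives the same initials for the person trained in EMDR.
- **Data collector.** Data management gives those initials again for the person "responsible for collecting the data will be trained to monitor the data collection process at all stages of the study". Two other team members are named there, but only to monitor entry into SPSS.
- **Blinding.** The Blinding paragraph states that "it is impossible to blind either the participant or researchers". The Discussion repeats that "owing to the nature of the intervention, blinding is impossible in this study".
- **Outcomes.** Under Primary outcome: "The primary outcomes are the pain intensity, anxiety, or distress in patients with primary dysmenorrhea and their cognition of the dysmenorrhea". Under Measures, all three instruments are self-ratings. For the VAS, "The patient marks the severity of pain on the line"; the SUD "is a self-reporting scale with a 0- to 10-point rating scale"; and of the VOC the article says "Similar to the SUD scale, it is self-reporting".
- **Comparator.** Number of intervention sessions says that controls receive no intervention and are only asked to report their usual ways of relieving pain.

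**The concern.** In an open trial with subjective outcomes, it matters who receives the ratings. Here only one arm has a relationship with that person. The therapist works with treated women to put the idea of less painful or painless menstruation in place of their negative cognition (Intervention, Phases 3 and 5). If she then also collects their follow-up ratings, some women may rate their pain a little lower out of courtesy to her. Controls have no such reason.

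Such a shift acts in one direction and differs by arm. In the data it looks the same as a treatment effect, so neither the planned repeated-measures ANOVA nor any other model can remove it. It has to be prevented by how the data are collected.

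The blanket statement on blinding makes this worse because it closes the question. Participants and therapist indeed cannot be masked when EMDR is compared with nothing. It does not follow that the therapist must handle the outcome forms, or that the analyst must know which arm is which.

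**Working it through.** The document gives no figure for this bias, so there is none to reproduce. The check sets the statements side by side.

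1. **Same person in both roles?** Yes. The initials under Intervention, Treatment fidelity and Data management are identical.
2. **Is someone else assigned to outcome collection?** No. The two other named team members monitor data entry, which comes after the rating has been given.
3. **Does contact with the collector differ by arm?** Yes. Six sessions of 30 to 90 minutes give 6 × 30 = 180 minutes to 6 × 90 = 540 minutes, or 3 to 9 hours, for a woman who attends all of them. Early responders may have fewer sessions. A control has none.
4. **Can the outcomes be influenced by the person rating?** Yes, all three. The participant marks the VAS herself, so the route is social desirability and not assessor scoring.
5. **Is separation feasible with what the plan already has?** Yes. Randomization and allocation gives every participant a unique code, Data management names two team members other than the therapist, and Trial status says that recruitment had not begun.
6. **How much of the bias would separation reach?** Only the part that comes from reporting to the therapist. Participants still know their group and still rate themselves, so expectation effects stay.

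**Generic illustration, not attributable to this defect.** It shows only how sensitive a trial of this size is to a reporting shift from any source. Inputs: 41 per group (Sample size calculation), no true effect, and a two-sided 5% t test on one follow-up score with 80 degrees of freedom. The shift of b standard deviations is assumed. The noncentrality is b × √(41/2) = 4.53 × b.

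| Assumed shift b (SD) | Noncentrality | Significant results |
|---|---|---|
| 0 | 0 | 5% |
| 0.1 | 0.45 | 7% |
| 0.2 | 0.91 | 15% |
| 0.3 | 1.36 | 27% |
| 0.5 | 2.26 | 61% |

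The plan uses repeated-measures ANOVA and does not say which term is tested, so its own rates would differ. Nothing in the document says what share of any shift would come from the therapist collecting the forms.

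**The case against.** The strongest objections are these.

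- **The hand-over is inferred.** The article makes this researcher responsible for collecting and monitoring data. It does not say how forms are returned, whether the VAS is marked in her presence, or whether forms carry names. Participants have codes and are assured of confidentiality, and a condensed article may leave form logistics to the full protocol. This stands as a limit on wording: treated women *may* report to their therapist. It does not remove the point, because the role assignment itself is stated.
- **The bias cannot be abolished.** This stands. A reader might infer that separating collection would make the comparison unbiased. It would not, since participants know their group and the comparator is no intervention.
- **The percentages do not measure this defect.** This also stands. A reader might infer from the illustration that the false-positive rate here is, say, 15% or 27%. The document does not support that: the shifts are assumed totals from any cause, and the test is not the planned one.
- **Masking the analyst does nothing about self-report bias, and the article does not say who analyses.** Both are true. Coded arm labels protect something else, namely choices made after seeing data, such as acting on the normality check or choosing post hoc tests. They are a small addition to the main remedy.
- **The lack of blinding is disclosed.** It is, in Blinding and again in the Discussion. Disclosure does not justify an exposure that can be avoided, and calling all blinding of researchers impossible is broader than the facts require.

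**Conclusion.** The point holds in limited form. One researcher is both therapist and person responsible for data collection, in an open trial against no intervention whose primary outcomes are all self-reported. This leaves room for a courtesy bias that differs by arm, favours EMDR and can be avoided. The Blinding paragraph wrongly treats all researchers alike.

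The size of the bias cannot be derived from the document. Its direction rests on two assumptions: that follow-up ratings reach the therapist, which the role assignment suggests but does not spell out, and that women are inclined to please the person who treated them. The remedy reduces bias and leaves the expectation component in place. Planned sample size, alpha and power are unaffected. The change should be made before recruitment because the bias cannot be corrected afterwards.

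**What to change.** 1. **Follow-up ratings, both groups.** Have participants complete the VAS themselves, together with any SUD and VOC ratings used for the between-group comparison. They return these under their study code, in a sealed envelope or by online form, to the team members already named for data-entry monitoring. The therapist neither receives nor handles them.
2. **In-session ratings.** SUD and VOC scores taken during EMDR sessions stay with the therapist as part of the therapy and are not used as the between-group outcome.
3. **Analysis.** Keep the arms as coded labels in the SPSS file until the primary model has been run. Participant codes follow the allocation sequence from 1 to 88, so the list linking code to arm should be kept away from the analyst.
4. **Blinding paragraph.** Restate it by role: participants and therapist unblinded, outcome forms not handled by the therapist, analyst masked. Amend the matching sentence in the Discussion, and add that expectation bias from participants knowing their group remains a limitation.

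Cost: slight effort to chase forms. No extra staff or visit is needed.

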### Ethical and safety issues

The research protocol has been reviewed and approved by the human ethics and research committee of Qazvin University of Medical Sciences (reference number: IR.QUMS.REC.1397.100). It has also been registered in the Iranian Registry of Clinical Trials (IRCT20180823040851N1 in 2018-10-06).

In addition, the following ethical considerations will be respected during the research: obtaining informed consent from the students, the voluntary nature of the participation in this research, and the ability to withdraw from the study at any time. At the beginning and end of the study, the participants will be assured that all of the collected data are completely confidential, and their identity will remain anonymous in any presentations and publications arising from this study. In addition, before the commencement of the first treatment session, the participants will be provided with a brief explanation of EDMR therapy. The research goals will be shared with them and they will be informed of the significance of their cooperation, which will help those suffering from similar thoughts and negative emotions due to dysmenorrhea. The criteria for performing the clinical trial will be considered in the research. Furthermore, EMDR therapy will be freely available to the participants in the control group on request after the completion of this study.

## Discussion

The present study will be the first randomized clinical trial to investigate the effect of EMDR therapy on pain management in patients with primary dysmenorrhea. The results are expected to provide insight into the safety and efficacy of EMDR therapy in treating primary dysmenorrhea. The strength of the study is its design as a randomized method with good sample size. However, owing to the nature of the intervention, blinding is impossible in this study.

EMDR therapy is a systematic, comprehensive, non-invasive, simple, and evidence-based treatment for unpleasant memories and related events [29]. EMDR therapy has been used to treat various conditions, including anxiety, depression, chronic pain, phantom limb pain, somatization syndrome, and post-traumatic stress disorder syndrome [30–34]. The systematic review by Tesarz et al. (2014) showed that EMDR therapy was effective, safe, and promising in treating chronic and uncomplicated pain [35]. The present study was designed on the basis of the efficacy of EMDR therapy shown in previous study in the management of a range of conditions, including chronic pain and previous unpleasant memories. In the present study, the focus is on the chronic nature of primary dysmenorrhea and the correlation between the trauma due to the initial unpleasant experience of menstruation and associated psychosomatic disturbances, such as anxiety and depression and dysmenorrhea.

### Trial status

Recruitment has not yet begun. However, all necessary permissions have been acquired. The estimated date of recruitment is October 27, 2019. The expected date for completing the recruitment is December 30, 2019.

## Data Availability

Analyzed data and materials will be de-identified and published.

## Abbreviations

CONSORT: Consolidated Standards of Reporting Trials
EMDR: Eye movement desensitization and reprocessing
SUD: Subjective Units of Anxiety or Distress Scale
VAS: Visual analogue scale
VOC: Validity of Cognition Scale
